## Abstract

**Background:**

An arteriovenous fistula (AVF) is the preferred vascular access for hemodialysis treatment. After creation many of the AVFs will never mature or if functioning will need an intervention within 1 year due to an AVF stenosis. Studies investigating possible therapies that improves the AVF maturation and survival are scarce. Far infrared therapy (FIR) has shown promising results. In minor single centre and industry supported trials FIR has shown improved AVF maturation and survival. There is a need of a randomized multicentre controlled trial to examine the effect of FIR on the AVF maturation and survival and to explore the possible AVF protective mechanism induced by the FIR treatment.

**Methods:**

This investigator initiated, randomized, controlled, open-labeled, multicenter clinical trial will examine the effect of FIR on AVF maturation in patients with a newly created AVF (incident) and AVF patency rate after 1 year of treatment in patients with an existing AVF (prevalent) compared to a control group. The intervention group will receive FIR to the skin above their AVF three times a week for 1 year. The control group will be observed without any treatment. The primary outcome for incident AVFs is the time from surgically creation of the AVF to successful cannulation. The primary outcome for the prevalent AVFs is the difference in number of AVFs without intervention and still functioning in the treatment and control group after 12 months. Furthermore, the acute changes in inflammatory and vasodilating factors during FIR will be explored. Arterial stiffness as a marker of long term AVF patency will also be examined.

**Discussion:**

FIR is a promising new treatment modality that may potentially lead to improved AVF maturation and survival. This randomized controlled open-labelled trial will investigate the effect of FIR and its possible mechanisms.

**Trial registration:**

Clinicaltrialsgov NCT04011072 (7th of July 2019).

## Background

Worldwide, the number of patients with end stage kidney disease in need of hemodialysis therapy increases [1]. In order to receive an efficient hemodialysis treatment, the patient needs a well-functioning and stable vascular access. Currently, there are 3 options: an arteriovenous fistula (AVF), an arteriovenous graft (AVG) and a central venous catheter (CVC) [2, 3]. CVCs are associated with an increased risk of stenosis of the central thoracic vessels, thrombosis in a present AVF, local and systemic infections and death [4–7]. In a multivariate analysis performed by Bray et al., patients with a tunneled CVC almost had a 7 fold increased risk of death from septicemia compared with patients with an AVF [4].

AVGs are associated with increased risk of infection, stenosis in the AVG and loss of access [6, 8, 9]. A study by Almasri et al. [9] showed the need of an intervention (defined as both surgical and endovascular) during 2 years of observation to be 60% in the AVG group compared to 45% in the AVF group. Conclusively, the AVF is the preferred vascular access. However, the AVF is not without complications. Following the creation of an AVF there is a 20–50% risk of maturation failure and consequently, the AVF cannot be used [10, 11]. Furthermore, up to 45–67% of the AVFs will develop a stenosis, that needs an intervention within 1 year [9, 10]. During the period with a malfunctioning AVF, the patient may need a CVC as an alternative vascular access which leads to an increased risk of infection, more hospital days and death [6]. The poor AVF maturation and patency is due to many factors. High age, female sex, anatomic location of the AVF (primarily radio-cephalic), small vein diameter, comorbidity, surgeon experience and perhaps arterial stiffness, are all risk factors that influence the AVF survival [10, 12–15].

Studies investigating possible therapies that improves the AVF maturation and AVF survival are scarce as stated in the vascular access guidelines by European Renal Best Practice and European Society for Vascular Surgery [2, 3]. Furthermore, it is not well established, what causes the neo-intimal hyperplasia in the AVF leading to stenosis and loss of the vascular access [16, 17]. This makes it even more difficult to clarify potential treatments.

Far Infrared therapy (FIR) is a new treatment modality modestly suggested by the European Renal Best Practice to improve AVF maturation and patency [18]. Although suggested, they also call for further studies of FIR, which should be multicentre, preferably blinded and non-industry supported.

FIR is an electromagnetic radiation (heat therapy), that is given directly on the skin above the AVF. The infrared light has in various animal models shown to have a thermal effect, which leads to vasodilatation and angiogenesis [19]. In the clinical setting, FIR is used for wound healing and peripheral ischemia, where it has shown beneficial effect [20]. FIR also promotes a non-thermal effect, where it inhibits vascular endothelial inflammation via induction of anti-inflammatory and vasodilating factors, such as Heme-oxygenase and Nitric oxide [19, 21]. The non-thermal effect is sparsely investigated and understood, especially in hemodialysis patients.

The effect of FIR on the AVF maturation and survival has been explored in a few studies [22–25]. Lin et al. [22, 23] showed a significant improvement in the maturation (90% vs 76% at 3 months) in patients with a newly placed AVF. In patients with a well-functioning AVF with no prior interventions, a lower incidence of AVF malfunction during 12 months of treatment with FIR compared with a control group was found (13% vs. 30%). Lai et al. [24] compared patients in a FIR group with a control group with more than 2 previous interventions on the AVF or AVG. They found a significantly improved unassisted patency rate for the AVGs (16% vs 2%), but not for AVFs (25% vs. 18%). All these studies were randomized, but not blinded. They were performed in one single dialysis department in Taiwan and has not been reproduced or confirmed in other dialysis units and populations.

A study by Choi et al. [25] designed to examine the effect of FIR on cannulation pain and access flow, found no difference in the AVF survival in the FIR treatment group compared to a control group during 12 months of intervention. However, the study was not powered to address this issue. Interestingly, the study showed a significant decrease in the cannulation pain. In conclusion, FIR appears as a promising treatment for AVF maturation and perhaps AVF survival, but the data is inconsistent. There is an urgent need for further investigations of the possible effects of FIR.

The present paper describes the design and rationale of a randomized, controlled, open-labeled multicenter trial of the effect of FIR on AVF maturation and on number of AVFs without intervention still functioning after 1 year. Changes in anti-inflammatory and vasodilating factors during FIR treatment will be explored and arterial stiffness as a marker of AVF maturation and survival will be examined.

## Objectives

To evaluate if treatment with FIR for 40 min three times weekly for 1 year will improve the AVF maturation (time to successful cannulation) on newly placed AVFsTo evaluate if treatment with FIR for 40 min three times weekly for 1 year will improve the overall AVF patency in prevalent and incident AVFsTo evaluate if FIR suppresses inflammatory factors and improve vasodilating factors after one FIR treatment for 40 minTo evaluate if arterial stiffness measured by pulse wave velocity can be used as a marker for AVF maturation and patency.

## Methods and design

### Study design and setting

The FAITH on Fistula trial is a randomized, controlled, open-labeled, multicenter clinical trial. The study design is shown in Fig. 1. The study takes place in a total of 9 dialysis units within the eastern part of Denmark. The dialysis units provide hemodialysis treatment for approximately 1000 hemodialysis patients [26]. All new AVFs will be created by experienced vascular surgeons at 2 hospital departments. Standard criteria’s to assess the arterial and vein adequacy, such as ultrasound, vein diameter > 3 mm, the patients clinical status are used by the vascular surgeons according to the guidelines [2, 3, 27]. Because of the many dialysis units included in the study, the adequate participant enrolment is not difficult to obtain.

### Interventions

Ws Far Infrared Therapy Unit, model TY-102F (medical Device Class 11a CE0434, FIRAPY, New Taipei City, Taiwan) is used for the intervention (Fig. 2). The patients in the intervention group will receive FIR above the skin of the AVF for 40 min three times a week for 1 year during a HD treatment. The FIR emitter will be placed 20 cm above the skin surface in the area of the AVF. Every FIR treatment will be registered in the patient chart. The control group will not receive any FIR during the study time, but except from this they will be followed exactly as the intervention group. If the nurses are in doubt of application of the FIR treatment (eg. Hematoma, infection), the primary investigator will be contacted to evaluate the AVF and make the decision.

**Fig. 2 Fig2:**
[figure not shown]
Picture of a enrolled patient receiving FIR treatment on his arteriovenous fistula (informed consent is given)

### Outcomes

The primary endpoint for the prevalent AVFs is the difference in the overall patency rate between the treatment and control group after 12 months. The overall patency rate is defined as the AVFs without intervention and still in function after 1 year of treatment.

The secondary outcomes are the difference after 12 months in the treatment and control group in: access flow, number of abandoned AVF, change of vascular access to CVC or a new AVF, cardiac output, cannulation pain and number of patients with steal syndrome. Additional secondary outcomes are cardiac output and arterial stiffness at baseline as markers for AVF patency. Finally, the acute changes in the inflammatory and vasodilating factors after one FIR treatment will be compared to changes in the control group.

The primary endpoint for the incident AVFs is the time from placement of an AVF to successful cannulation (defined as a successful hemodialysis treatment with two fistula needles placed in the AVF). The secondary outcomes is the difference between the treatment and control group after 12 months in: number of interventions, diameter of the AVF measured by ultrasound, number of abandoned AVF, number of vascular access change (CVC or new AVF), number of primary patency, change in access flow, change in cardiac output, cannulation pain and number of patients with steal syndrome. Additional secondary outcomes are cardiac output and arterial stiffness at baseline as markers for AVF maturation and patency.

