### Study visits

Baseline demographic data will be collected from the patient’s hospital file. Subsequent visits will be performed monthly for 12 months. After 12 months the FIR treatment will be ended, but both groups will be followed additionally 6 months. End of study will be at 18 months after baseline. The study visit, procedure and data collection are outlined in Table 2. Participants will be followed until end of study or lost to follow-up, defined by death, change of renal replacement therapy, change of vascular access, if the participant moves away or withdraw their consent. If a patient wish to withdraw their consent, an effort will be made to keep the patient in the study.

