### Data collection and management

The data collection and timeline are shown in Table 2.

At baseline the following data will be collected:
Demographics, including renal diagnosis, length of end stage kidney disease, dialysis vintage and previous transplantation.Comorbidity.MedicationPre-study AVF information (previous AVF, anatomic placement of current AVF, AVF vintage, number of interventions on previous and present AVF, cannulation technique, access flow, recirculation, ultrasound of the AVF (cross section in millimetre).Pre-study hemodialysis information: hemodialysis/hemodiafiltration, dialysis prescription, Kt/V, anticoagulants during hemodialysis, median blood flow rate, arterial and venous pressure, blood pressure and weight in the latest 3 hemodialysis treatments before baseline, nutritional status defined by the normalized protein catabolic rate.For newly created AVFs: acute or permanent CVC, preoperative vein diameter and peroperative accessflow.Pre-study side effects: cannulation pain (visual analog score), dialysis side effects, symptoms of steal syndrome.Blood samples: haemoglobin, haematocrit, thrombocytes, leucocytes, C-reactive peptide, urea, creatinine, albumin, INR, ionized calcium, phosphate, parathyroid hormone, 25-OH D_2_, fibroblast-growth-factor-23, up-uc-MGP.

Monthly, the following data will be collected:
Dialysis information: Dialysis prescription, Kt/V, intravenous iron since last visit, anticoagulant during hemodialysis.Side effects: Same as baseline and side effects of FIR

The ultrasound examination of the AVF will be performed with Transonic System Inc. HDO3 (Transonic, Ithaca, NY, USA) or Philips Affinity 70 G (Phillips, Andover MA, USA). Access flow and recirculation, will also be measured by Transonic System Inc. HDO3 or Philips Affinity 70 G. Cardiac output will be measured by Transonic System Inc. HCO3. Mobil-O-Graph (IEM, Stolberg, Germany) is used to measure the arterial stiffness.

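### Cannulation pain is scored monthly, but its between-arm comparison is worded as a 12-month difference; a repeated-measures analysis would use the data already collected and keep early leavers

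*Protocol article*

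**What the plan says.** **Collection.** The Data collection and management section of the protocol article lists at baseline "Pre-study side effects: cannulation pain (visual analog score), dialysis side effects, symptoms of steal syndrome". Under the heading "Monthly, the following data will be collected" it then gives "Side effects: Same as baseline and side effects of FIR", so the visual analogue pain score recurs every month. Study visits adds: "Subsequent visits will be performed monthly for 12 months".

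**Comparison.** For prevalent AVFs, Outcomes says "The secondary outcomes are the difference after 12 months in the treatment and control group in" a list that includes "change of vascular access to CVC or a new AVF, cardiac output, cannulation pain and number of patients with steal syndrome". The incident list has the same 12-month time point. There, access flow and cardiac output are worded as changes, but cannulation pain is not.

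**Tests.** Sample size and statistics names paired and unpaired t-tests for normally distributed continuous variables, and the signed rank and Mann-Whitney tests otherwise. Kaplan-Meier and log-rank methods are reserved for patency. No repeated-measures model and no summary over visits is named.

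**End of follow-up.** Under Study visits, follow-up stops early at death, change of renal replacement therapy, change of vascular access, moving away or withdrawal of consent.

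**The concern.** If the comparison is made on the month-12 score, each completer contributes one on-treatment reading to the test between arms, and the other monthly readings do not enter it. That costs precision on an outcome for which neither cohort was sized.

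It also costs patients. Anyone who leaves before month 12 contributes nothing, even after many months of scores on allocated treatment. The loss may not be neutral, because a change of vascular access ends follow-up, is itself a listed outcome, and is something FIR is hoped to influence. The month-12 set is therefore partly selected by a variable that treatment may affect.

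The Background gives a reason to care about precision. An earlier FIR study designed around cannulation pain and access flow reported significantly less cannulation pain, while finding no difference in AVF survival.

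**Working it through.** **Plan's own figures.** None is given for pain. The two primary-endpoint sizes reproduce (two-sided 5%, 80% power), but this point does not rest on them:
- Prevalent, 35% vs 10%, pooled variance: [1.960 × √(2 × 0.225 × 0.775) + 0.842 × √(0.35 × 0.65 + 0.10 × 0.90)]² / 0.25² = 42.6, so 43 per group as stated.
- Incident, 100 vs 70 days, SD 46: 2 × 46² × (1.960 + 0.842)² / 30² = 36.9, so 37 per group as stated.

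**What enters a month-12 comparison.**
- Readings: 1 of 12 monthly scores per completer; 11 of 12 (92%) stay outside the between-arm test.
- Patients, prevalent: 52 per arm × (1 − 0.20) = 41.6, about 42.
- Patients, incident: 82 / 2 = 41 per arm; 41 × 0.80 = 32.8, about 33, before allowing for AVFs that are never cannulated.

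**Precision gained by averaging months 7-12.** Assume six complete readings with equal variance and equal correlation r, an effect that is constant over those months, and no baseline adjustment. The variance of the mean relative to one reading is (1 + 5r)/6. The article gives no r, so a range is shown.

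| r | Variance factor | SE ratio | SE smaller by | Equivalent to this many times the patients |
|---|---|---|---|---|
| 0.3 | 0.417 | 0.645 | 35% | 2.4 |
| 0.5 | 0.583 | 0.764 | 24% | 1.7 |
| 0.7 | 0.750 | 0.866 | 13% | 1.3 |
| 0.9 | 0.917 | 0.957 | 4% | 1.1 |

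**With baseline adjustment** (possible for prevalent AVFs). Assume baseline has the same correlation r with every later score. The ratio of the two adjusted variances, six-reading mean to single reading, is [(1 + 5r)/6 − r²] / (1 − r²). This gives 0.36, 0.44, 0.51 and 0.56 at r = 0.3, 0.5, 0.7 and 0.9. Under this simple correlation structure the gain no longer fades at high r, because adjustment removes the stable between-patient part and averaging removes much of the rest.

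**Detectable difference, for illustration.** With 42 per prevalent arm and one unadjusted reading, the difference detectable at 80% power is (1.960 + 0.842) × √(2/42) = 0.61 SD. Multiplying by the SE ratios gives 0.39, 0.47, 0.53 and 0.59 SD at the four correlations.

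**The case against.** **The analysis plan may supply a longitudinal model.** This is a condensed article, the SAP is not shown, and the visit table is an image. A reader might infer that the plan prescribes one reading and throws the rest away. The article does not say so; that is the plain reading of its time point and tests, and no more. The same 12-month phrase also heads cumulative items such as abandoned AVFs, where it must mean the treatment year. Still, the article is not silent: it states a time point and a set of tests, and a pain score, unlike a count of events, does not accumulate.

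**Paired tests are named as well.** It would be wrong to say that only two-sample tests are offered. Paired tests, however, compare readings within patients, not arms. The named tests could be applied to a per-patient average, but no such average is defined.

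**The monthly scores may have another use.** The Monitoring section reviews side-effect incidence every third month, and pain is filed under side effects. It therefore cannot be said that the scores go unused, only that they do not enter the between-arm test.

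**Pain has no special standing.** A reader might infer that pain is the only outcome on which earlier FIR work showed an effect. The Background does not support that: it also reports significantly better maturation in another controlled FIR study, and it gives no access-flow result for the study that found less pain.

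**The gain may be small and the remedy has limits.** At r = 0.9 without baseline adjustment the gain is about 4%. A fixed 12-month contrast is a legitimate choice. Pain does not exist for an abandoned AVF, or for an incident AVF before its first cannulation. A mixed model averaged over months 7-12 implicitly treats leavers as if cannulation had continued. Restricting incident patients to those cannulated conditions on the primary endpoint of that cohort. The trial is open-label, and a narrower interval does not correct biased self-report. These points stand. They shape the fix and limit its weight, but they do not favour a month-12 test that faces the same selection with fewer data.

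**Conclusion.** The point holds as an efficiency and missing-data weakness in a secondary outcome. On the plain reading, the between-arm comparison of pain uses the month-12 score, leaves out the earlier monthly scores and excludes patients whose follow-up ended sooner.

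The size depends on an unknown within-patient correlation. Without baseline adjustment and with complete readings, the standard error of a six-reading mean is 4% to 35% smaller across r = 0.9 to 0.3. Equal correlation and a constant effect over months 7-12 are further assumptions. Using leavers' earlier scores should add some information, which is not quantified here.

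No stated figure is wrong, and neither primary endpoint is touched.

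**What to change.** - Analyse all monthly pain scores recorded while the study AVF is in use, with a mixed model for repeated measures. For prevalent AVFs, adjust for baseline pain.
- Report the between-arm difference averaged over months 7-12 as the main estimate, with the month-12 contrast from the same model beside it.
- State the estimand as pain while the AVF is being cannulated, and say how scores are handled once an AVF is abandoned or before it is first cannulated.
- For incident AVFs, label the comparison descriptive, because it conditions on successful cannulation.

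**Cost.** A few lines of analysis code and one sentence in the outcome definition; no new data. The downside is small: the main estimate describes the second half-year rather than month 12 alone, it relies on missing at random for leavers, and it leaves open-label reporting bias where it was.

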### Study visits

Baseline demographic data will be collected from the patient’s hospital file. Subsequent visits will be performed monthly for 12 months. After 12 months the FIR treatment will be ended, but both groups will be followed additionally 6 months. End of study will be at 18 months after baseline. The study visit, procedure and data collection are outlined in Table 2. Participants will be followed until end of study or lost to follow-up, defined by death, change of renal replacement therapy, change of vascular access, if the participant moves away or withdraw their consent. If a patient wish to withdraw their consent, an effort will be made to keep the patient in the study.

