### Sample size and statistics

#### Prevalent AVFs

Al-jaishi et al. and Almasri et al. [9, 10] found a primary patency rate and assisted patency rate for AVFs after 1 year to be 60–69%. Lin et al. found a decline in the incidence of interventions from 30 to 12% after 1 year in the FIR group compared to the control group [23]. We wish to detect an improvement in the overall patency rate and therefore a decline from 35 to 10% in the number of prevalent AVFs with at least one intervention or without function after 1 year of treatment. The 10% is chosen since Lin’s study is from 2007 and we suspect an improved vascular surgery, perhaps with a reduced incidence in interventions. With a power of 80% and a significance of 5% we need 43 patients in each group. With an expected drop out of 20%, the number is 52, resulting in a total of 104 patients for the prevalent AVF group.

Because of the inhomogeneous group in the prevalent AVFs, the patients will be stratified according to previous interventions in the data analysis.

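### Change of vascular access is classed as loss to follow-up, although an AVF-related change is a primary-endpoint failure for prevalent AVFs and a secondary outcome in both cohorts

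*Protocol article*

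**What the plan says.** Study visits sets the end of follow-up: "Participants will be followed until end of study or lost to follow-up, defined by death, change of renal replacement therapy, change of vascular access". Moving away and withdrawal of consent complete the list. Study end is otherwise 18 months after baseline.

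Outcomes defines the primary endpoint for prevalent AVFs: "The overall patency rate is defined as the AVFs without intervention and still in function after 1 year of treatment". The 12-month secondary outcomes for that cohort include "number of abandoned AVF, change of vascular access to CVC or a new AVF". Those for incident AVFs include "number of vascular access change (CVC or new AVF".

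The sample size section for prevalent AVFs plans for "a decline from 35 to 10% in the number of prevalent AVFs with at least one intervention or without function", so loss of function lies inside the planned failure rates. It continues: "With a power of 80% and a significance of 5% we need 43 patients in each group". Drop-out is then a separate allowance: "With an expected drop out of 20%, the number is 52".

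The statistics text names a chi-squared test for categorical variables, and Kaplan-Meier curves with a log-rank test for patency. It does not say whether an access change is an event or a censoring time.

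**The concern.** One event has three roles. For prevalent AVFs, a fistula replaced by a CVC or a new AVF because it failed is no longer in function, so the patient fails the primary endpoint. In both cohorts the patient also contributes to a secondary outcome. Under Study visits the same patient is lost, in the same list as someone who moves away.

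If the label is followed, loss depends on the outcome. Failures that begin with an access change leave both numerator and denominator, and under the planning rates more of them leave the control arm. Patency is overstated in both arms, the absolute difference shrinks, and abandonment and access change risk being undercounted. Censoring these patients in the Kaplan-Meier analysis would not help, because it censors at the moment of failure.

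For incident AVFs the point is limited to patients whose study fistula is abandoned or replaced. Their access change is a secondary outcome, yet they are labelled lost.

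**Working it through.** **Inputs.** From the prevalent sample size section: failure rates 35% (control) and 10% (FIR), 80% power, 5% significance, 43 per arm, and 52 per arm after the drop-out allowance. Allocation is 1:1. Sidedness is not stated; two-sided is assumed.

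**Plan's own figure.** Pooled two-proportion formula, with mean rate (0.35 + 0.10)/2 = 0.225:

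n = [1.960 × √(2 × 0.225 × 0.775) + 0.842 × √(0.35 × 0.65 + 0.10 × 0.90)]² / 0.25² = (1.157 + 0.474)² / 0.0625 = 42.6, so 43 per arm.

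The stated 43 is reproduced, with power 80.4%. The 52 is 43 × 1.2 = 51.6, rounded up. The planned power therefore needs access-change failures to be counted within the 35% and 10%.

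**Effect of the label.** Let f be the share of failures whose first event is an access change before month 12. An AVF with an earlier intervention has already failed and is not affected. The documents do not give f, so a range is assumed, equal in both arms. If these patients are dropped:

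- observed failure rate: p′ = p(1 − f)/(1 − fp)
- patients left in the arm: n′ = n(1 − fp)

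Example, f = 1/3 from 43 per arm:

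- control: 0.35 × 0.667/(1 − 0.1167) = 0.264, with 43 × 0.883 = 38.0 patients left
- FIR: 0.10 × 0.667/(1 − 0.0333) = 0.069, with 43 × 0.967 = 41.6 patients left
- share of patients removed: 11.7% of controls and 3.3% of FIR patients

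Power uses the same pooled two-sided test with the reduced rates and numbers.

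| f | Control vs FIR failure | Difference (points) | Power from 43 per arm | Power from 52 per arm, no other drop-out |
|---|---|---|---|---|
| 0 | 35.0% vs 10.0% | 25.0 | 80% | 87% |
| 10% | 32.6% vs 9.1% | 23.6 | 77% | 84% |
| 20% | 30.1% vs 8.2% | 21.9 | 73% | 80% |
| one third | 26.4% vs 6.9% | 19.5 | 66% | 74% |
| 50% | 21.2% vs 5.3% | 15.9 | 55% | 63% |

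The 43 column assumes that other drop-out has already used up the allowance. The 52 column is the favourable bound, where access change is the only loss.

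**The case against.** The strongest reply is that Study visits says only when follow-up ends. It defines no analysis set. An access change is known when it happens, so follow-up could stop because the outcome has occurred and been recorded, and an analysis plan not shown could count it as a failure. This stands in part. A reader might infer that the article excludes these patients, or runs the chi-squared test on completers only; it says neither. What remains is that the article gives an explicit definition of loss that conflicts with its own endpoints. An analysis plan can reclassify the event, but it cannot recover later measurements if data collection stopped there.

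A reader might also infer that follow-up of incident patients ends when they move from the CVC to the study fistula, since that too changes the access in use. The documents do not support this. Outcomes glosses access change for that cohort as a CVC or a new AVF, meaning a move away from the study fistula. Data collection and management also requires access flow to be measured after successful cannulation.

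On size, f has no source in the documents. Part of the planning evidence concerns interventions, and a patient with an earlier intervention has already failed, so f may be modest. Starting from 43 after linking these patients to the drop-out allowance would count some of them twice. Both objections stand, which is why the table shows a range and both starting numbers. At f of 20% or less from 52 per arm, power stays at 80% or above.

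**Conclusion.** The point holds as a contradiction in the text: the same event is a loss to follow-up in Study visits, a failure of the prevalent primary endpoint in Outcomes and the sample size section, and a secondary outcome in both cohorts. Applied as written, the rule makes loss outcome-dependent, overstates patency and shrinks the difference between arms.

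The size is conditional. Over f from 10% to 50%, the planned 25-point difference becomes 23.6 to 15.9 points. Power is 77% to 55% from 43 evaluable per arm, or 84% to 63% from 52 per arm with no other loss. These figures assume a two-sided test, the planning rates, the same f in both arms, and that the affected patients are dropped, which is the ordinary consequence of the label but not a rule the article states. Only access changes before month 12 that are the first failure event affect the prevalent primary endpoint.

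**What to change.** 1. Remove change of vascular access from the definition of loss to follow-up.
2. State that AVF abandonment, or an AVF-related change to a CVC or a new AVF, is a patency failure on its date, both in the 12-month comparison and in the planned Kaplan-Meier curves. It is neither censored nor missing.
3. Count the same event in the access-change and abandonment secondary outcomes of both cohorts.
4. Keep following these patients for the outcomes that can still be measured. Some, such as flow or diameter of the study fistula, lose their meaning once it is abandoned.

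Replacing the 12-month comparison of proportions with a Kaplan-Meier estimate is optional and not needed to resolve the conflict.

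The cost is protocol and analysis wording. Data are already collected at regular dialysis sessions, so continued follow-up adds little burden.
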